### Randomisation, allocation and blinding

The randomisation sequence was computer generated and used permutated blocks (4 or 6 participants per block). The allocation sequence is concealed at all times throughout the study. The computer generation and allocation were performed by a statistician, external to the study team. Upon enrolment, an infant is assigned to the next number on the appropriate stratified list. Each unique number is assigned to one of the eight treatment alphabets (see below). Treatment groups are stratified by age (≤6 or >6 months), site (Darwin or Townsville) and requirement (yes or no) for oxygen at point of randomisation. The importance of excluding older children and stratifying at the 6 month age group is well described[30,34]. A placebo medication ensures that all children, carers, researchers, hospital staff, and clinic staff are blinded to treatment group until analyses of the data.

The placebo medication has been specifically manufactured by the Institute of Drug Technology (IDT) Australia Limited (Melbourne, Vic) which has a similar taste and colour to azithromycin. The azithromycin medications were repackaged by IDT. Thus both the azithromycin and placebo are in identical opaque bottles and sealed with an aluminium foil. For both, equal volumes of water are added using a syringe and needle by punching the seal.

Eight alphabets (N, O, P, Q, R, S, T, U) were used for the bottles of azithromycin and placebo medications (4 alphabets each). We used multiple alphabets rather than sequential numbers on the bottles to allow storage of extra bottles of trial medications in clinics for the day-7 and day-14 doses. This was necessary in the context of our study setting (children mainly from remote Indigenous communities), to enhance availability and administration of trial medications once the child has been discharged from the hospital.

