### Data collection

All data are recorded on standardised forms. Demographic information (age, gender, region, birth details, smoke exposure, breast feeding, household size, etc) and medical history are obtained from the primary care-giver and the medical charts. The primary and secondary outcome measures (see below) are monitored twice daily until the hospital admission's end-point is reached (ready for respiratory discharge, defined as >16-hours without supplemental oxygen and infant is feeding well). Clinical assessment data include oxygen requirement and level, physiological measurements for clinical severity score (respiratory rate, accessory muscle use, degree of wheeze),[27] other physiological measurement (temperature, heart rate), requirement and duration of other therapies required (intravenous fluids, nutritional support, antibiotics), ear examination findings (signs of suppuration) and subsequent pneumonia (diagnosed by the independent treating 'blinded' paediatrician). In addition, the results of routine investigations (full blood count and chest radiographic findings) are recorded. On day-21, the presence of cough, wheeze and auscultatory abnormality on clinical review are documented. Adverse effects (vomiting, diarrhoea, rash) are also documented.

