### Sample size

We plan to enrol 200 Indigenous infants. In our retrospective study,[6] the mean LOS in Indigenous infants with bronchiolitis at RDH was 96 (SD 24) hours. The mean duration of supplemental oxygen requirement in Indigenous infants with bronchiolitis was 36 (SD 14) hours. For a mean difference of 24-hours in LOS between groups (power = 90%, α = 5%) the required sample size is 23 per group. The numbers to detect a 12-hour difference in supplemental oxygen requirement is 30 per group. These are large effect sizes but more conservative estimates than seen in the Turkish study[26]. In that study,[26] the difference between groups was 30-hrs for LOS and 31-hours for supplemental oxygen requirement. Assuming similar effects, a sample size of at least 100 in each sub-age group is also sufficient for an *a-priori *subgroup analysis based on age (power of 90% and 2-tailed α of 5%). If the effects are smaller, we will have an 80% power to detect a difference of 10-hours in LOS in all infants and an 80% power to detect a difference of 14-hours in LOS in the ≤6-months age group. We do not believe that smaller benefits than this would be sufficient to change clinical practice.

For the most important secondary outcome (readmission rate for a respiratory illness within 6-months of discharge), the power of our study to detect a reduction from 30% to 10% is 95% (5% significance). This is a large effect but consistent with the reduction described in the Turkish study (75% reduction)[26]. At 80% power we will be able to detect a reduction in readmission rates from 30% to 13%. For our other secondary outcomes, accurate sample size estimations are not possible given the lack of any relevant data.

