### Statistical analysis and reporting

Data will be reported and presented in accordance with the updated CONSORT criteria[40]. Children will be analysed according to allocation status (regardless of subsequent management). An interim analysis is planned and the data safety and monitoring committee will determine if the study should be ceased should superiority of azithromycin be identified after 70% of sample size is achieved.

The primary outcomes (LOS and duration of supplemental oxygen requirement) will be compared between infants receiving placebo or azithromycin using unpaired Student's T-tests or Mann-Whitney tests (depending on normality of distribution). Although we expect randomisation to equally distribute potential confounding factors between each of the groups, we will examine the distribution of known confounders between groups (eg. birth weight, smoke exposure status in-utero and postnatal, breast feeding, etc). Should baseline data differ between groups, regression will be used to check that the primary outcomes are not affected by this chance finding. An *a-priori *sub-analysis will compare infants aged ≤ 6-months with those aged >6-months.

When examining the efficacy of azithromycin at reducing readmission rate for respiratory illness (Secondary Aim-2), the Odds Ratio (OR) between groups will be calculated. The OR will also be used to compare additional antibiotic use between groups. The number needed to treat (NNT) (for benefit), 95% CI will be described if any significant differences are found. If significant, NNT for harm will be calculated for adverse events. For Secondary Aim-3 (short-term impact of azithromycin on macrolide-resistance of pathogens in NPS cultures): the proportions of children with penicillin-non-susceptible *S. pneumoniae *and macrolide-resistant *H. influenzae *spp and *M. catarrhalis *before and after trial medications will be compared using ORs and 95% CI. Descriptive data will be utilised for Secondary Aim-4 (point prevalence of respiratory viruses and other respiratory pathogens).

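### Numbers needed to treat and to harm are reported only after a significant test, so a real excess of adverse events could often receive no between-arm estimate

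*Protocol article*

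**What the plan says.** All the rules are in the protocol article, under Statistical analysis and reporting.

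- **Benefit:** "The number needed to treat (NNT) (for benefit), 95% CI will be described if any significant differences are found".
- **Harm:** "If significant, NNT for harm will be calculated for adverse events".
- **Readmission for respiratory illness:** "the Odds Ratio (OR) between groups will be calculated", with no condition on significance.
- **Additional antibiotic use:** "The OR will also be used to compare additional antibiotic use between groups", also unconditional.
- **Resistance in nasopharyngeal cultures:** proportions compared by odds ratios with 95% CIs, unconditional.

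Under Data collection, the harms are named: "Adverse effects (vomiting, diarrhoea, rash) are also documented". No odds ratio, risk difference or interval is named for them; the conditional NNH is all there is. The Sample size section gives power for the two primary durations and for readmission. It says that the other secondary outcomes could not be sized, and it states neither expected rates nor power for adverse events.

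**The concern.** Reporting an absolute effect only once it crosses 5% has two consequences.

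First, non-significant results drop out. A trial sized on length of stay, oxygen and readmission may well have little power for vomiting, diarrhoea or rash. A real excess would then often miss significance, and under the stated rule it would get neither an estimate nor an interval. A reader could take that as absence of harm when the data are compatible with a material excess.

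Second, results that pass a significance filter are larger on average than the truth when power is low, so the NNT or NNH shown is on average too small.

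The Discussion expects conclusive results to change treatment guidelines. Readers will therefore need to weigh benefit against harm on an absolute scale, including where the harm estimate is imprecise. This is a rule that the article states, so it is not a detail left to an analysis plan that is not shown.

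**Working it through.** **Inputs from the document**

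- Total size: "We plan to enrol 200 Indigenous infants".
- Allocation: the ratio is not stated in words. I take 1:1, hence 100 per arm, which fits the equal number of bottle letters ("azithromycin and placebo medications (4 alphabets each").
- Significance level: 5%. Two-sidedness is stated for the age-subgroup calculation and assumed throughout.
- Readmission: 30% versus 10% with 95% power, and 30% versus 13% with 80% power.

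**Assumed inputs.** The document gives no adverse-event rates and does not name the test for them. I use a range of rates and a pooled-variance two-proportion z test (equivalent to the uncorrected chi-square).

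**Step 1: reproduce the stated power.** Power = Φ{[d − 1.96·√(2p̄(1−p̄)/n)] / √[(p1(1−p1) + p2(1−p2))/n]}, where d = p1 − p2 and p̄ is the mean of the two rates.

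For 30% versus 10%, n = 100, p̄ = 0.20: (0.200 − 0.1109)/0.0548 = 1.627, and Φ = 94.8%, against 95% stated. For 30% versus 13% the same formula gives 83.8%; with a continuity correction it is 79.1% and by Fisher's exact test 80.0%, against 80% stated. The article's figures therefore reproduce with 100 per arm.

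**Step 2: how often the rule yields an NNH, and how large the effect looks when it does.** I enumerated every possible pair of event counts with 100 per arm. For each true pair of rates I summed the probability of significance in the true direction and took the mean risk difference (RD) among those significant results. NNT or NNH = 1/RD.

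| True rates | Significant | No NNT/NNH | True RD (points) | Mean RD when significant | True NNT/NNH | 1/(mean RD) |
|---|---|---|---|---|---|---|
| Adverse event 10% vs 5% (assumed) | 27% | 73% | 5 | 9.5 | 20 | 10.5 |
| Adverse event 12% vs 5% (assumed) | 44% | 56% | 7 | 10.4 | 14 | 9.6 |
| Adverse event 20% vs 15% (assumed) | 15% | 85% | 5 | 13.2 | 20 | 7.6 |
| Adverse event 20% vs 10% (assumed) | 52% | 48% | 10 | 13.8 | 10 | 7.2 |
| Readmission 30% vs 10% (planned) | 96% | 4% | 20 | 20.5 | 5.0 | 4.9 |
| Readmission 30% vs 13% (planned) | 85% | 15% | 17 | 18.6 | 5.9 | 5.4 |
| Readmission 30% vs 20% (assumed) | 37% | 63% | 10 | 16.2 | 10 | 6.2 |

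Fisher's exact test lowers the chance of significance further: to 19% at 10% versus 5%, and to 34% at 12% versus 5%.

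**Step 3: what one non-significant result would hide.** Take events in 18/100 versus 10/100. Then p̄ = 0.14 and z = 0.08/√(2 × 0.14 × 0.86/100) = 1.63, so p = 0.10 and the rule gives no NNH. The risk difference is +8 points, with a 95% CI (Newcombe) of −1.7 to +17.8. The upper limit corresponds to an NNH of 1/0.178, about 6. An interval that wide is what a reader needs to see.

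**The case against.** The strongest reply is that the article conditions one derived statistic and nothing else. It does not say that counts by arm will be withheld, it promises CONSORT reporting, and a condensed article may leave safety tables to a fuller document. This stands. A reader might infer that a non-significant harm would leave no figure at all, or that no absolute effect could be seen without significance. The text does not support that, because adverse events are recorded and nothing bars tabulating them by arm. What remains is that the only between-arm comparison named for harms is switched off by a non-significant test.

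A second reply is that benefit is covered. It largely is: readmission and additional antibiotic use have an odds ratio regardless of the result. A reader might also infer that every NNT reported would be materially biased. At the article's own readmission scenarios that is not so (4.9 against 5.0, and 5.4 against 5.9). The inflation is material only for smaller effects and low-powered outcomes.

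Third, the adverse-event rates are mine. Nothing in the document shows that an excess of harm is likely; the calculation shows only what would happen if there were one.

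Fourth, an NNT has an awkward interval when the risk-difference CI spans zero, because it passes through infinity. That is a fair reason to restrict the NNT, but not to leave the risk difference and its CI unnamed.

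Finally, unconditional reporting would not alter the NNT in a trial that does reach significance. Correct: the gain is that the other results are shown as well.

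**Conclusion.** The point holds in limited form. Both NNTs are tied to significance, and for adverse events the conditional NNH is the only between-arm measure named, in a trial that states no power for them. If a true excess of 5 to 10 points existed, the rule would produce no NNH in roughly 48% to 85% of trials across the assumed rates, with 100 per arm and a two-sided 5% pooled test. Overstatement of the reported NNTs is real at low power and negligible at the planned 30% versus 10%.

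This is a minor reporting flaw. The primary outcomes are durations that do not use the NNT, and the sample size, randomisation and data collection are untouched.

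**What to change.** Replace the two conditional sentences under Statistical analysis and reporting with:

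*For readmission, additional antibiotic use and each adverse event, counts by arm and the absolute risk difference with 95% CI will be reported whether or not the difference is significant. NNT or NNH may be added as a re-expression where the CI excludes zero.*

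The planned odds ratios can stay alongside. An NNT with an interval should not be demanded in every case, for the reason given above. The cost is one sentence and a few extra table columns, with no new data. The drawback is that intervals for rare events will be wide, which is a fair statement of what 200 infants can show about harm.

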### Aims of the study

Our primary research question is: Amongst hospitalised Indigenous infants with bronchiolitis, does azithromycin (compared to placebo) improve clinical outcomes (length of stay in hospital and duration of oxygen supplementation)? Our primary hypothesis is that: The anti-microbial and anti-inflammatory properties of the macrolide, azithromycin, will improve the clinical outcomes of Indigenous infants hospitalised with bronchiolitis.

Our secondary aims are:

2. To determine the effect of azithromycin on readmissions into hospital within 6 months of treatment;

3. To assess the short-term impact of azithromycin on macrolide resistance patterns of respiratory bacterial pathogens in the nasopharynx; and

4. To describe the point prevalence and diversity of respiratory viruses, *Mycoplasma pneumoniae *and Chlamydia species using sensitive molecular diagnostic techniques.

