### Intervention and follow up

If eligibility is fulfilled and after informed consent has been obtained, the infant is randomised to receive either a single, oral liquid dose of azithromycin syrup (30 mg per kg) or an equivalent volume of placebo. Medication is given within 24-hours of hospitalisation. Infants randomised to the intervention arm of the study will receive additional treatment doses of azithromycin syrup (30 mg per kg) on day-7 and day-14. Those randomised to the control arm receive an equivalent volume of the placebo syrup. The later doses will be either supervised by study nurses or administered by families with phone support on the day the medication is due. Final clinical follow up will occur in the local health clinic on day-21 (or closest available date from day 20 to 24).

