### Specimen collection

A single nasopharyngeal swab (NPS) specimen for respiratory virus and other potentially important respiratory pathogen (*M. pneumoniae, Chlamydia *spp) testing is collected from each subject at enrolment. In addition, NPS is repeated before hospital discharge for bacterial culture and antibiotic susceptibility testing, as per our laboratory research protocol (see below)[35,36].

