### Laboratory methods

#### Bacteriology of NPS

Culturing, identifying and serotyping common respiratory bacteria from NPS is an established technique in our laboratory at Menzies in Darwin[35]. Swabs are stored in SMGGB at -80°C before being batch processed for typical respiratory bacterial pathogens, notably *H influenzae and *non-typeable *H influenzae*, *M. catarrhalis *and *S. pneumoniae*. Batches of swabs are thawed and 10 μL aliquots cultured overnight on selective media at 37°C in 5% CO_2_. Growth of *S. pneumoniae*, *H. influenzae *and *M. catarrhalis *is recorded and confirmed. Four isolates each of *S. pneumoniae *and *H. influenzae *and two isolates of *M. catarrhalis *per positive swab are tested for anti-microbial resistance and stored[35,37]. *S. pneumoniae *isolates are serotyped using the Quellung method (antisera from Statens Serum Institute, Denmark).

In addition to routine susceptibility testing using the calibrated dichotomous susceptibility (CDS) disc diffusion method, azithromycin minimum inhibitory concentration (MIC) will be determined using Etest (AB Biodisk, Sweden) if the azithromycin disc annulus is less than 6 mm. For *S. pneumoniae*, the penicillin MIC is determined for penicillin non-susceptible isolates (oxacillin and/or penicillin disc annulus <6 mm) and for *H. influenzae*, the ampicillin MIC is determined for isolates if the ampicillin disc annulus is less than 6 mm. Interpretive criteria (CSLI breakpoints) used for *S. pneumoniae *are penicillin non-susceptible MIC > 0.12 μg/mL, azithromycin resistant MIC ≥ 2 μg/mL, and for *H. influenzae*, ampicillin resistant MIC ≥ 4 μg/mL, azithromycin resistant MIC > 4 μg/mL. Beta-lactamase activity will be determined for *H. influenzae *and *M. catarrhalis *isolates.

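### The Aim-3 resistance analysis leaves out macrolide-resistant pneumococcus, states no between-arm contrast, and describes as post-treatment a discharge swab that typically follows one of three doses

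*Protocol article*

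**What the plan says.** The protocol article, under Aims of the study, gives the third aim as "To assess the short-term impact of azithromycin on macrolide resistance patterns of respiratory bacterial pathogens in the nasopharynx". Statistical analysis and reporting restates it as the "short-term impact of azithromycin on macrolide-resistance of pathogens in NPS cultures" and then lists what will be analysed. For S. pneumoniae this is "the proportions of children with penicillin-non-susceptible" isolates; macrolide resistance is named only for H. influenzae and M. catarrhalis. These proportions "before and after trial medications will be compared using ORs and 95% CI".

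Other sections bear on that sentence:

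- Bacteriology of NPS sets a pneumococcal criterion of "azithromycin resistant MIC ≥ 2 μg/mL", and Secondary laboratory outcomes lists resistance to macrolides as well as to penicillin.
- Specimen collection says "NPS is repeated before hospital discharge for bacterial culture and antibiotic susceptibility testing". It describes the enrolment swab as being for viruses, M. pneumoniae and Chlamydia. The Abstract names enrolment and discharge as the swab times, and no later swab is described.
- Intervention and follow up places the second and third doses "on day-7 and day-14". Randomisation, allocation and blinding explains that bottles are stored in clinics so that these doses can be given once the child has left hospital.
- Sample size gives a mean stay of 96 h (SD 24).

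**The concern.** Three mismatches sit in one sentence.

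**Endpoint.** Penicillin non-susceptibility does not answer a question about macrolides. The pneumococcal macrolide data will exist, but the stated comparison does not use them.

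**Contrast.** Change from before to after is not the effect of azithromycin. Under Recruitment, enrolled infants may receive other therapies apart from macrolides, and additional antibiotic use is itself an outcome, so carriage of resistant strains can shift in both arms. Only the comparison with placebo separates azithromycin from those influences.

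**Exposure.** If the later swab usually follows only the first dose, describing it as following the trial medications invites a conclusion about three doses that the data cannot support.

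The Discussion calls resistance monitoring an important safety component, so a reader may rely on this analysis for reassurance.

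**Working it through.** The article states no rate, sample size or power for Aim 3, so there is no Aim-3 figure to reproduce.

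**1. Check on the stay figures.** The planned size for a 24 h difference with SD 24, 90% power and two-sided 5% is 2 × (1.960 + 1.282)² × 24²/24² = 21.0, so 22 per group. The t-test version gives 22.02, so 23, which matches the stated 23. This confirms that SD 24 was the planning value; it does not test the mean.

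**2. Share of discharge swabs taken before the day-7 dose.** Day 7 is counted as 168 h from admission. The first dose may be given up to 24 h into the stay, so if days run from that dose, the count understates the share.

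- Normal shape: (168 − 96)/24 = 3.0, giving 99.9%.
- Lognormal shape: s² = ln(1 + (24/96)²) = 0.0606; μ = ln 96 − 0.0303 = 4.534; (ln 168 − 4.534)/0.246 = 2.40, giving 99.2%.

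Primary outcomes warns that actual discharge may lag behind readiness for discharge but gives no figure. The delays below are therefore assumptions.

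| Assumed mean delay | Before day 7, SD 24 | Before day 7, SD 48 |
|---|---|---|
| none | 99.2–99.9% | 92–93% |
| 24 h | 96–98% | 84–86% |
| 48 h | 84% | 69–74% |
| 72 h | 50–53% | 50–56% |

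Ranges run over the normal and lognormal shapes. For day 14 (336 h), the normal shape gives at least 99.98% of swabs before the third dose in every row.

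**3. Why the contrast matters.** OR = [p₁/(1 − p₁)] / [p₂/(1 − p₂)]. All rates here are assumed, to show only that the two contrasts answer different questions.

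- Resistant carriage 10% at entry and 20% at discharge in both arms: before/after OR = (0.20/0.80)/(0.10/0.90) = 2.25; between-arm OR at discharge = 1.0. The change would be credited to azithromycin wrongly.
- 10% at entry in both arms, then 10% on azithromycin and 5% on placebo: before/after OR on azithromycin = 1.0; between-arm OR = (0.10/0.90)/(0.05/0.95) = 2.11. A difference between arms would not show.

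With 100 per arm, power for the second case is about 27%, so the interval would matter more than the test.

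**4. Endpoint.** No arithmetic applies. The aim, the restated aim, the laboratory criterion and the declared outcome all include macrolide resistance without excluding pneumococcus. Only the analysis sentence leaves it out.

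**The case against.** The strongest reply is that this is loose drafting in a condensed article. Much of that reply is sound.

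- **Contrast.** A reader might infer that the plan discards the placebo group. It does not say so: the same section states that children are analysed by allocation, and the sentence is introduced as the impact of azithromycin. Before and after proportions by arm may well be intended. What remains is that no between-arm contrast is stated here, while the sentences on readmission and antibiotic use state one.
- **Pairing.** A reader might infer that odds ratios ignoring the two swabs per child will be used. The text says only odds ratios with intervals; a matched odds ratio would fit it, and the choice can be left to the analysis plan.
- **Baseline culture.** A reader might infer that there are no baseline data. The Abstract's reference to development of resistance, the unrestricted culture methods, the resistance subgroup under Secondary clinical outcomes and the before proportion itself all point to an enrolment culture. Specimen collection is merely out of step with them.
- **Pneumococcus.** Nothing in the article ranks it above the other two organisms, so its omission cannot be called the loss of the main signal. Penicillin non-susceptibility is a legitimate outcome in its own right.
- **Timing.** No section says the swab precedes doses two and three; this is inferred from the planning stay, and delayed discharges could move some swabs past day 7. An early swab also suits a short-term aim. Neither point makes the description of the swab accurate.

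**Conclusion.** The point holds in a limited form: the Aim-3 analysis sentence does not match its aim.

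- The omission of macrolide-resistant S. pneumoniae is plain on the text.
- The contrast is ambiguous, and taken literally it is not the randomised comparison.
- The exposure description is inaccurate for nearly all infants on the planning figures: about 99% of later swabs would follow one dose of three. With an assumed mean delay of up to 48 h and SD 24, the share is still about 84% or more. At longer delays or wider spread, a substantial minority or about half could follow the second dose, but almost none the third.

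The timing result rests on the retrospective mean and SD and on assumed distribution shapes and delays. The odds ratios are illustrations from assumed rates and do not show that this trial's result would be biased.

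The correction should be made. The outcome is a secondary laboratory one without a power claim, and the primary outcomes do not depend on it.

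**What to change.** In Statistical analysis and reporting, for Secondary Aim 3:

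1. Make the endpoint the proportion of children with macrolide-resistant S. pneumoniae, H. influenzae and M. catarrhalis, and keep penicillin-non-susceptible S. pneumoniae as a separate outcome.
2. State the contrast as azithromycin versus placebo at the discharge swab, by odds ratio with 95% CI, adjusted for enrolment carriage of the same organism where the enrolment culture is available.
3. Describe the later swab as taken *at hospital discharge (typically after the first dose)*, and limit the resistance conclusion to that exposure. A statement about the full course would need a swab after the third dose, which the article does not describe.
4. Reconcile Specimen collection with the Abstract, the resistance subgroup and the analysis sentence on whether the enrolment swab is cultured.

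Items 1 to 3 change wording only; they need no new visit or procedure. Item 4 is a clarification if enrolment culture is already planned. If it is not, there is laboratory cost, and the suitability of the stored swabs must be confirmed first: the bacteriology section names a storage medium for cultured swabs, while the virology section says only that swabs are frozen.
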